### Aim of the study

This study will attempt to answer the question, "does mass distribution of the nicotine patch actually work (i.e., increase quit rates significantly above those who do not receive free nicotine patches)?" By conducting a randomized controlled trial of free mass NRT distribution, this study will evaluate the efficacy of the mass distribution approach. Comparison of an experimental group which will be offered free nicotine patches to a control group that does not get offered nicotine patches will determine whether or not mass distribution of NRT is an effective way of helping smokers quit. It is hypothesized that among eligible Canadian smokers expressing interest in receiving free nicotine patches, those randomly selected to be offered 5 weeks of free nicotine patches will exhibit a significantly greater quit rate at 8 weeks and 6-month follow-ups compared to those not offered free nicotine patches (saliva cotinine measurements used to validate self-reported smoking abstinence). Previously it has been shown that those who metabolize nicotine more quickly have significantly poorer cessation rates on nicotine patch than slow metabolizers [13]. Therefore this study will also explore whether fast nicotine metabolizers (as measured by the 3-Hydroxycotinine/cotinine ratio) will be less likely to succeed at quitting smoking, as compared to slow nicotine metabolizers, when offered free nicotine patches. Finally, the study will investigate how compliance with recommended amount of NRT, and whether prior use of NRT, affects success at quitting smoking when smokers are offered free nicotine patches.

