#### Content of 8-week and 6-month follow-up interviews

At 8-week and 6-month follow-ups, subjects who have not quit will be asked how many cigarettes per day they currently smoke and their intentions to quit smoking; how soon after waking they smoke their first cigarette; and if, since their baseline interview, they have stopped smoking for even one day because they were trying to quit. Subjects in the experimental condition will be asked to evaluate their experiences with NRT and to elaborate on their efforts to quit smoking. Specifically, at 8-weeks subjects will be asked if they received the NRT; how soon after receipt they began to use it; how much of it (if any) they used; if relevant, why they did not use any or all of it; whether or not they experienced any withdrawal symptoms and which ones; and what challenges they encountered to quitting/reducing. At 6-months, subjects will be asked whether or not they purchased additional NRT to help in their quit effort (what type and how much); whether or not they plan to purchase more NRT to quit or maintain their non-smoking; if they have smoked in the past 30 days or reduced from baseline, what benefits they have noticed; what supports they had for quitting; and what additional resources they sought to help them quit. These questions will be asked after the core smoking status outcome measures have been assessed. Subjects in the control condition will also be asked about their use of NRT but the questions will be framed to reflect purchase of NRT from sources other than this ongoing study. Subjects in both conditions will also be asked about their use of other smoking cessation aids.

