### Data Analysis

#### Power analysis

Quit rates for those who use nicotine patches have been obtained from several sources, including systematic reviews by Fiore et al. [26] and a Cochrane review by Stead and colleagues [16]. Both these reviews indicate a 10% increase in tobacco cessation rates upon using nicotine patches as compared to placebo at 6-month follow-up. This 10% increase is roughly in concordance with the 30 day point prevalence rate for abstinence observed at the 6-month follow-up point of the STOP mass distribution demonstration trial (9%; note that this trial had no control group so the results reflect pre-post changes in smoking rates) [12]. However, we recognize that both of these estimates are probably too large for a pragmatic randomized controlled trial because the impact of interventions is often smaller in real world settings (and pre-post estimates, such as those found in the STOP Study, can also be inflated). Thus, we have chosen to power our trial based on the assumption that our quit rate will be half as large (i.e., a 5% increase in quit rates in the experimental condition versus the control at 6-month follow-up). Finally, we can estimate a 3.7% baseline rate of smoking cessation at 6-month follow-up in a general population sample using findings from the 2008 Canadian Tobacco Use Monitoring Survey (CTUMS) [3]. Given these results, we predict that the subjects in the control condition will display a 3.7% quit rate and subjects in the experimental condition will display a 8.7% quit rate at 6-month follow-up.

Using these assumptions, a power analysis was conducted; this indicated that a total of 403 respondents would be needed per condition to detect a 5% difference at a significance level of .05 with a power of 80% (estimate calculated with continuity correction factored in) [27]. Thus, we have chosen an ideal sample size of approximately 800 respondents in order to conduct appropriate analyses.

Based on our previous research using a similar research design, albeit with problem drinkers rather than smokers [28,29], a 20% attrition between baseline and 6-month follow-up can be expected (the most important follow-up for this study); this would mean that a sample size of 1,000 respondents would be needed at baseline to take part in the randomized trial. Similar follow-up rates have been obtained for smokers in the Ontario Tobacco Survey, indicating that a 20% attrition rate estimate is also reasonable for smokers [30].

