#### Analysis Plan

The primary analyses will employ manual stepwise logistic regressions. Specifically, dependent measures will be 30 day point prevalence abstinence at 6-month follow-up and 7 day point prevalence abstinence at 8-week follow-up. Separate logistic regression analyses will be conducted for each time point (validated by saliva cotinine sample). In the primary analyses, subjects lost to follow-up will be assumed to be active smokers. In Step one of the logistic regression, experimental condition will be entered as a dummy coded variable (0 = control condition; 1 = experimental condition). This step will test the primary hypothesis regarding the impact of sending free NRT on quit rates. Steps two and three of the logistic regression will involve adding interaction terms to test the mediator and moderator hypotheses (3-HC/cotinine ratio, compliance with NRT use, prior use of NRT; main effects terms entered in Step two and interaction terms entered in Step three). Sex difference analyses will be conducted in a similar manner (i.e., is there an interaction effect of subjects' sex by receipt of NRT on abstinence rates at 6-month follow-up?). As part of these primary analyses, we will also conduct a chi-square test to explore whether there is differential loss to follow-up between experimental conditions. Further we will replicate the primary analyses with all subjects with missing data excluded from the analyses. If the results are the same between the analyses where the missing data is excluded and where subjects lost to follow-up are assumed to still be current smokers, then we can safely assume that there is no differential attrition between conditions (or, at least none that impacted on the outcome of the trial).

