Subgroup analyses will examine quit rates among subjects within the experimental and control conditions who: (a) are slow versus fast nicotine metabolizers as measured by the 3-HC/cotinine ratio; (b) report using all 5 weeks of the free NRT they were sent as compared with those who do not use all 5 weeks; (c) had used NRT for a quit attempt at least once before participation in the proposed study as compared with those who had never used NRT before; and (d) are male or female (to assess any interaction by sex). Further, we will compare subjects in the experimental condition who used the NRT to just those subjects in the control condition who did not use any NRT during the same time period (i.e., they did not obtain NRT from other sources). Finally, using just the baseline data (N = 1,000), we will relate the 3-HC/cotinine ratio to patterns of smoking and prior use of NRT.

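### The comparison of full-course patch users with the rest cannot show that compliance affects quitting, because relapse is itself a reason to stop; it should be labelled descriptive

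*Protocol article*

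**What the plan says.** The Analysis Plan lists four subgroup analyses of quit rates. Three group subjects by baseline characteristics: nicotine metabolism, prior NRT use and sex. Subgroup (b) instead groups subjects who "report using all 5 weeks of the free NRT they were sent as compared with those who do not use all 5 weeks". Controls are sent no patches, so this contrast lies wholly inside the experimental arm.

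The purpose is given in the Aim of the study section: to learn "how compliance with recommended amount of NRT, and whether prior use of NRT, affects success at quitting smoking". The Analysis Plan also counts compliance among the variables for which the regression involves "adding interaction terms to test the mediator and moderator hypotheses".

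The section on the follow-up interviews says that experimental subjects will be asked at 8 weeks whether the patches arrived, when they started, how much they used and, "if relevant, why they did not use any or all of it". The protocol does not use these answers in forming subgroup (b), does not place relapse before or after stopping, and does not limit the comparison to a descriptive reading.

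**The concern.** Completing the course is not a baseline trait. It is observed over the same five weeks in which most early relapse would be expected. Someone who returns to smoking in week 2 and puts the patches away falls into the non-completer group as a consequence of failing to quit. Randomisation gives no protection, because both groups come from the same arm.

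A higher quit rate among completers therefore has at least two explanations: finishing helps people quit, or failing to quit makes people stop. The contrast cannot tell them apart, yet the stated aim adopts the first. What is at stake is the answer to a named secondary question, not the main result.

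**Working it through.** **The plan's own figure.** The protocol gives no figure for subgroup (b). Its related figure is the sample size, which predicts that "subjects in the control condition will display a 3.7% quit rate and subjects in the experimental condition will display a 8.7% quit rate" and states that "403 respondents would be needed per condition to detect a 5% difference at a significance level of .05 with a power of 80"%, with the "estimate calculated with continuity correction factored in". With p1 = 0.037, p2 = 0.087, mean 0.062 and d = 0.05, two-sided:

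- n = [1.960·√(2·0.062·0.938) + 0.842·√(0.037·0.963 + 0.087·0.913)]² / 0.05² = 364
- corrected n = (364/4)·[1 + √(1 + 4/(364·0.05))]² = 403

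This matches, and nothing below changes it.

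**Inputs for the check.**

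- q = 8.7% abstinent at 6 months in the experimental arm (Power analysis).
- r = share relapsing within 5 weeks: assumed, 50% to 70%.
- f_r and f_n = shares of relapsers and of non-relapsers who finish all 5 weeks: assumed, from 40% and 60% up to 20% and 80%.
- Finishing has no effect on quitting, and everyone abstinent at 6 months is among those who had not relapsed by week 5: assumed.

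**Formulas.**

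- Share finishing: C = r·f_r + (1 − r)·f_n
- Quit rate in completers: q·f_n / C
- Quit rate in non-completers: q·(1 − f_n) / (1 − C)

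**Results with a true effect of zero.**

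| r | f_r | f_n | C | Completers | Non-completers | Ratio |
|---|---|---|---|---|---|---|
| 0.5 | 0.4 | 0.6 | 0.50 | 10.4% | 7.0% | 1.5 |
| 0.6 | 0.3 | 0.7 | 0.46 | 13.2% | 4.8% | 2.7 |
| 0.7 | 0.2 | 0.8 | 0.38 | 18.3% | 2.8% | 6.5 |

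Middle row: C = 0.6·0.3 + 0.4·0.7 = 0.46; 0.087·0.7/0.46 = 13.2%; 0.087·0.3/0.54 = 4.8%. The ratio does not depend on q, because q cancels.

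**Using a figure from the documents.** The Background reports 15% abstinent at end of treatment in the Ontario programme. Take this as the share not relapsed (r = 0.85). If 30% of abstainers and 50% of relapsers stop early, C = 0.85·0.5 + 0.15·0.7 = 0.53, and the rates are 11.5% against 5.6%, ratio 2.1. If 20% and 80% stop early, C = 0.29, and the rates are 24.0% against 2.5%, ratio 9.8. The stopping rates are again assumed.

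**When the bias vanishes or reverses.** If stopping is unrelated to relapse (f_r = f_n), both groups show 8.7%. If abstainers stop early more often than relapsers (60% against 40%, still with 15% abstinent), C = 0.85·0.6 + 0.15·0.4 = 0.57. Completers then show 0.087·0.4/0.57 = 6.1% and non-completers 0.087·0.6/0.43 = 12.1%, so finishing would look harmful.

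**Why restricting to subjects not yet smoking when they stopped is no remedy.** Completers would have to stay abstinent through week 5, early stoppers only up to the week they stopped. With 60% relapsing by week 5 at a constant weekly hazard (assumed), the share still abstinent at week t is 0.4^(t/5). With no effect of finishing, the quit rate is q/0.4 in completers and q/0.4^(t/5) in those who stopped at week t. The false ratio is 0.4^(t/5 − 1): 2.1 for stopping at week 1 and 1.2 at week 4.

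**The case against.** The Analysis Plan, read alone, only says that quit rates will be examined and compared. The causal verb is in the Aim of the study section, and the mediator and moderator language belongs to the regression. This is fair as to where the wording sits. But the aim is what the subgroup serves, and nothing restricts the comparison to description.

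A reader might infer that completers are bound to look far better even if finishing does nothing. The documents do not support that. They give no completion rate and no link between relapse and stopping. Some subjects may stop because they feel they no longer need the patches, which pushes the other way. Relapsers who quit again before 6 months would shrink the ratio.

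A reader might also infer that the trial would go on to report a benefit of finishing and so mislead policy on supply length. No section says so. The studies cited on duration compare different amounts supplied, whereas this trial sends one amount. The policy question in the Discussion is whether to supply free NRT, and that rests on the comparison by assignment.

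Finally, the reasons for non-use are already collected, and how they enter a secondary table may be set out in a fuller document. That stands as to detail. It does not cover a grouping and a causal aim that the article itself states, and the interview content described does not fix whether smoking resumed before or after the patches were stopped.

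**Conclusion.** The point holds for a stated secondary aim. Subgroup (b) selects on a self-reported variable, measured after randomisation, that the outcome can determine, so it cannot show that compliance affects quitting. With no true effect, the false ratio is about 1.5 to 6.5 over the assumed range. The spurious gap is about 3.5 points (10.4% against 7.0%, before rounding) to 15.5 points (18.3% against 2.8%), beside the 5-point difference the trial is powered to detect. Size and direction rest on assumed relapse and finishing rates.

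It would be wrong to read this as a threat to the main conclusion. The primary comparison is by assignment, whether or not the patches are accepted, and it and the sample size are unaffected.

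**What to change.** 1. State in the Analysis Plan that subgroup (b) describes an association and does not estimate an effect of finishing the course.
2. Add one item to the 8-week interview asking whether smoking had resumed before the patches were stopped. With the reasons already collected, report non-completers separately as declined or never started, stopped after return to smoking, and stopped for other reasons.
3. In the Aim of the study section, replace the causal verb with wording of association for compliance.
4. Base any causal statement about patch use on randomised assignment, for example a complier-average effect with assignment as instrument and its assumptions stated.
5. Do not build a compliance contrast on subjects who were not yet smoking when they stopped, since that adds survivor bias in favour of completers.

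The cost is one interview item and some rewording, with no change to the sample size, the arms or the primary outcome. The price is small subgroups and a weaker statement about compliance.

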## Methods/design

### Design

This is a single-blind, randomized controlled trial of mass distribution of free Nicotine Replacement Therapy to Canadian smokers. A two-stage recruitment process will be employed, in the context of a general population survey with two follow-ups (8 weeks and 6 months). Random digit dialing of Canadian home telephone numbers and an initial interview will identify households with adult (age 18 or over) smokers who smoke 10 or more cigarettes a day. One individual from each household who is willing to take part in a smoking study that involves three interviews, with saliva collection for 3-HC/cotinine ratio measurement at baseline and saliva cotinine verification at 8-week and 6-month follow-ups will be randomly selected (according to most recent birthday). Willing participants will be offered a $20 honorarium for completing the baseline and each of the 8-week and 6-month follow-ups. Verbal consent will be obtained as the initial contact is by telephone.

As part of the baseline survey, eligible subjects will be identified for the second stage of the recruitment process and will be randomized into experimental and control conditions to receive versus not receive nicotine patches. Eligibility will be determined by a series of questions regarding hypothetical interest in nicotine patches to quit smoking (including willingness to have nicotine patches sent to their home) and having no contraindications for using NRT. A randomized half of the eligible subjects will be assigned to the experimental condition and asked for their permission to have nicotine patches sent to their home. These subjects will have 5 weeks of nicotine patches sent to their homes to help them quit smoking. Subjects in the control condition will not be offered nicotine patches. Only subjects in the randomized controlled trial will be followed-up at 8 weeks and 6 months. See Figure 1 for a CONSORT diagram of the proposed study design.

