### Interventions

#### Experimental condition

A randomized half of the subjects meeting baseline criteria and expressing an interest in receiving free nicotine patches, willingness to use the Patches within a week to quit smoking, interest in having the patches sent to their home, and meeting criteria for eligibility to receive NRT (i.e., no health contraindications) will be randomly assigned to the experimental condition (the remainder will be assigned to the control condition). Subjects in the experimental condition will be asked, at the end of the baseline survey, if they want to be sent a free, 5-week supply of Nicotine Patches. Those who say "yes" will have the NRT mailed to their home the week after their baseline interview. As is employed in the Ontario mass distribution of NRT initiative [12], a 5-week program of nicotine patches will be sent (3 weeks of Step 1 [21 mg of nicotine]; 1 week of Step 2 [14 mg of nicotine]; 1 week of Step 3 [7 mg of nicotine]). Once randomly assigned to this condition, subjects will be counted as part of the experimental condition whether they agree to accept the NRT or not (intent-to-treat approach).

The 5-week program of nicotine patches was chosen for pragmatic reasons, which balanced a limited budget to supply the NRT and conduct a large population survey, and because of findings from literature regarding effective treatment duration. A recent Cochrane review evaluating the efficacy of NRT has revealed no differences in treatment effect between trials offering up to eight weeks of nicotine patch treatment and those offering longer treatments [16]. Furthermore, several trials evaluating usage patterns of free nicotine patches offered to smokers through a Smokers' Quitline have shown no differences in 7- and 12-month quit rates between individuals receiving 2, 4, 6, or 8-week supplies of free nicotine patches [17,18]. These findings however, are inconsistent with two other studies demonstrating higher quit rates among Smokers' Quitline callers receiving 8 weeks versus 2 weeks of free nicotine patches [19], and 6 weeks versus 4 weeks of free NRT [20]. Given the apparent inconsistencies in the literature surrounding effective treatment duration of mailed out free NRT, we chose a middle of the road approach of 5 week nicotine patch program.

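### The planned comparison of NRT users in the experimental arm with NRT non-users in the control arm is not protected by randomisation and can show a false benefit

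*Protocol article*

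**What the plan says.** The Analysis Plan section of the protocol article introduces its secondary comparisons with "Subgroup analyses will examine quit rates among subjects within the experimental and control conditions". After listing four subgroup splits, it adds that the investigators will "compare subjects in the experimental condition who used the NRT to just those subjects in the control condition who did not use any NRT" over the same period. It gives no adjustment, no causal method and no caveat on interpretation for this comparison.

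The primary analysis follows a different rule. Under Experimental condition, "subjects will be counted as part of the experimental condition whether they agree to accept the NRT or not (intent-to-treat approach"). In Step one of the logistic regression, randomised condition is the only term, and "This step will test the primary hypothesis regarding the impact of sending free NRT on quit rates". Subjects lost to follow-up are counted as smokers.

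The section on the 8-week and 6-month interviews shows that NRT use is self-reported at follow-up. Experimental subjects are asked about the patches they were sent, and control subjects about NRT obtained elsewhere.

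**The concern.** Smokers who open the parcel and use the patches are probably, on average, those who make a quit attempt. Control subjects who go out and obtain NRT are probably also attempters. The planned comparison removes the non-attempters from one arm and some of the attempters from the other. If that description is right, the two remaining groups differ in quit propensity before any effect of the patch.

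The Background section faults earlier evaluations of mass distribution because, without randomisation, they could not support a causal conclusion. This comparison has the same weakness inside a randomised trial. The Aim section says the study will look at how compliance affects success, and the Discussion addresses policy makers. A reader could therefore take the result as the effect of actually using the patch.

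**Working it through.** **1. The plan's own figures.** The power section predicts that "subjects in the control condition will display a 3.7% quit rate and subjects in the experimental condition will display a 8.7% quit rate". Its sample-size statement reads "a total of 403 respondents would be needed per condition to detect a 5% difference at a significance level of .05 with a power of" (the figure given there is 80%), and continuity correction is applied. The two-proportion formula with 3.7% versus 8.7%, two-sided 5% and 80% power gives 364 per condition without the correction and 403 with it, which matches. The plan says "a 20% attrition between baseline and 6-month follow-up can be expected", and 800 / (1 − 0.20) = 1,000 randomised. Since "A randomized half of the eligible subjects will be assigned to the experimental condition", that is about 500 per arm.

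**2. Inputs for the check.**
- From the document: 3.7% quitting and 500 per arm.
- Set to zero by design: the patch effect, so both arms quit at 3.7%.
- Assumed, not in the document: 50% NRT use in the experimental arm, 17% in control, and the strength of the link between use and quitting.

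**3. Model.** Let M be motivation, standard normal. Let q(M) be the quit probability, e(M) the probability of use in the experimental arm and c(M) in the control arm. Each is logistic in M, with intercepts set so that the averages are 3.7%, 50% and 17%. Then:
- experimental users quit at E[q·e] / E[e];
- control non-users quit at E[q·(1 − c)] / E[1 − c].

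Expected group sizes are 500 × 0.50 = 250 users and 500 × 0.83 = 415 non-users. The test is a pooled two-sided z-test at 5%. Use is taken as known for everyone.

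**4. Results with no patch effect.**

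| Log-odds per SD of M (quitting; use) | Experimental users | Control non-users | Difference (points) | Two-sided rejection |
|---|---|---|---|---|
| 0 (no link) | 3.7% | 3.7% | 0 | about 5% |
| 0.4; 0.5 (modest) | 4.0% | 3.6% | about +0.5 before rounding | about 6% |
| 0.8; 1.0 (strong) | 4.8% | 3.2% | +1.6 | about 19% |
| −0.3; 0.5 (negative) | 3.45% | 3.78% | −0.3 | about 5% |

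With strong links but higher uptake in the experimental arm, rejection falls to about 13% at 70% use and about 8% at 90% use.

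**5. A second model as a cross-check.** Here half of the subjects are motivated. Use is 80% in motivated and 40% in other subjects in the experimental arm, and 30% and 5% in control. Overall quitting is again 3.7% in both arms.
- If motivated subjects quit at 2, 5 or 10 times the rate of others, the comparison shows 4.1% versus 3.5%, 4.5% versus 3.3%, or 4.7% versus 3.2%.
- At ratio 5, selection on the experimental side alone gives +0.8 points, on the control side alone +0.4, and together +1.2. The two exclusions add up.
- With sharper selection (40% motivated; use 90% and 30%, then 40% and 5%) and ratio 10, it shows 5.6% versus 3.0%.
- At ratio 1 there is no difference. At ratio 1/3 the sign reverses, to 3.1% versus 4.0%.

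In this model, simulation of the intention-to-treat comparison stayed at 3.7% versus 3.7%, with about 2.5% false positives in each direction, in every scenario simulated.

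**The case against.** The strongest reply is that nothing primary depends on this comparison. The hypothesis is tested by randomised condition under an explicit intention-to-treat rule, the comparison sits with the subgroup analyses, and the document never calls it causal. All of that stands, and it limits the point to a secondary analysis.

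A second reply is that the size rests on assumptions. That also stands. The trial admits only smokers who say they would use the patch to quit and would start within a week. This may raise uptake and narrow the spread of motivation, and with modest links the rejection rate is close to nominal.

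A reader might infer three stronger claims, and the document supports none of them:
- **That a false benefit is certain whatever is assumed.** It is not. Bias is absent if use is unrelated to quit propensity and reverses if users are the harder-to-quit smokers. The eligibility section even hypothesises that prior NRT use goes with less success. That is a baseline trait and not use after randomisation, but it shows that the sign cannot be taken for granted.
- **That this will be the largest effect reported.** There is no basis for that. The planned split by completion of the five-week course could give a larger difference.
- **That false positives would run well above 19% on the strong-link assumptions.** A rate near 28% (about 8.3% versus 5.6%) needs overall quitting of about 6.5%, while the plan assumes 3.7% for controls.

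**Conclusion.** The concern holds in a limited form. The plan commits, without a caveat, to a comparison in which both groups are selected on self-reported behaviour after randomisation. The result cannot be read as the effect of NRT use, because its bias is unknown in size and sign.

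Upward bias is the more plausible direction, since using a patch, obtaining NRT and quitting all tend to go with making an attempt. At the plan's 3.7% quit rate, with 50% and 17% use, the false difference runs from about half a point (modest links, about 6% rejection) to 1.6 points (strong links, about 19%). The latter is about a third of the 5-point effect the trial is powered for (1.6 / 5 = 0.32). The sharpest selection in the second model gives 5.6 − 3.0 = 2.6 points from the rounded rates (2.7 before rounding), about half of it. The use rates and the strengths of the links are assumptions. The primary test, the sample size and the primary conclusion are not affected.

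**What to change.** Replace the comparison with a complier average causal effect: the intention-to-treat risk difference divided by the between-arm difference in the proportion using NRT. Randomised condition serves as the instrument, all randomised subjects are included, and a confidence interval is given. NRT use is already asked about in both arms, so no new data item is needed.

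The plan should also state:
- how NRT use is classified for those lost to follow-up (20% expected), since use is known only from interviews, with a sensitivity range over that choice;
- the assumption that the offer acts on quitting only through NRT use, with a note that an open offer may break it by prompting quit attempts without NRT.

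If the user versus non-user comparison is kept, it should be labelled exploratory and non-causal wherever it is reported.

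The cost is analysis-plan wording, a wider interval and reliance on the stated assumption. With the illustrative use rates, dividing by 0.50 − 0.17 = 0.33 makes the estimate and its interval about three times as large as the intention-to-treat ones. A true intention-to-treat difference of zero stays zero.
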